# TREATMENT OF SUBJECTS

## Intervention

Subjects will be asked to take 2 capsules/d containing either 100 mg MASQUELIER’s Original OPCs or the equivalent amount of mircocristalline cellulose (placebo) over the 8 weeks intervention period every morning before their breakfast with a glass of water.

## Use of co-intervention (if applicable)

During the intervention subjects are requested not to change their usual dietary habits. The use of any functional foods/ food supplements or other products containing vitamins, antioxidants, polyphenols is not allowed during the trial (see also in- and exclusion criteria (chapter 4.3 and 4.4).

## Escape medication (if applicable)

Not applicable.

# INVESTIGATIONAL PRODUCT

## Name and description of Investigational Substance

The Investigational Substance to be used in the current study is MASQUELIER’s® Original OPCs. MASQUELIER’s® Original OPCs is extracted from the seeds of *Vitis vinifera* grapes, and contains catechins and epi-catechins (single flavan-3-ols) and OPCs (oligomeric flavan-3-ol units; dimers to pentamers). Detailed analyses have established that the product is standardized to contain about 85% (w/w) flavan-3-ols (as established with the Vanillin-H2SO4 assay (48)) of which 50-60% (w/w) are single and dimeric flavan-3-ols (determined by HPLC) and void of polymeric proanthocyanidins. The Investigational Substance will be applied in capsules each containing 100 mg of MASQUELIER'S® Original OPCs.

Moreover, appropriate placebo capsules will be manufactured that only contains the bulk ingredient microcrystalline cellulose.

## Description and justification of route of administration and dosage

**Route of administration of Investigational Product:**

The Investigational Substance MASQUELIER’s® Original OPCs has been widely available as an oral dietary supplement in several markets around the world since the late 1980s. The same active ingredient has been officially registered and sold as an oral herbal medicine in France under the trademark name Endotelon® since 1978. In all the human intervention studies described above, the subjects were administered MASQUELIER’s® Original OPCs orally, with significant biological efficacy and very minimal adverse effects (no serious adverse events and few minor events such as gastric discomfort and one case of vertigo). Based on this, it proposed that the subjects will be administered MASQUELIER’s® Original OPCs dietary supplement via the oral route in the current study.

**Dosage of Investigational Product:**

The dosage of the Investigational Product proposed to be used in the current study is 200mg/day. As various human intervention studies conducted with MASQUELIER’s® Original OPCs used doses ranging from 100mg/day to 450mg/day for biological effects in reducing veno-lymphatic insufficiency, vascular fragility, microcirculatory abnormalities in the eye, UV-induced inflammation and for improving visual adaptation to glare. These doses were found to be highly efficacious in the studies, and no major adverse events and very few minor events were reported in a total of 5536 subjects involved in the studies. Of the 5536 volunteers, only 1 subject dropped out of the studies due to adverse effects attributed to intake of Investigational Substance MASQUELIER’s® Original OPCs. This subject complained of vertigo, which resolved after discontinuing Investigational Substance intake (74). In animal studies, the Investigational Substance MASQUELIER’s® Original OPCs, at doses of 50 mg/kg given orally for 21 days, was found to effectively reduce vascular permeability in rats (51). No apparent toxicity was observed at these effective doses in this study. Conversion of the animal doses to human equivalent doses (HED) based on body surface area gives doses of 480 mg/day (US FDA CBER Guidance Document, 2003).

Based on these observations, we decided to use a dose of 200mg/day of Investigation Substance MASQUELIER’s® Original OPCs in the current study.

# METHODS

## Study parameters/endpoints

### Main study parameters/endpoints

The main study parameters in the present trial will be the improvement of the flow mediated dilation (FMD) of the brachial artery as well as the endothelium-dependent and ‑independent reactivity of microvasculature in smokers during an 8-week consumption of daily 200 mg oligomeric proanthocyanidins (MASQUELIER’S® Original OPCs). Microvascular function will be assessed by means of Laser Doppler flowmetry (LDF) after local application of ACh, a combination of ACh and L-NMMA and SNP by iontophoresis

### Secondary study parameters/endpoints

Moreover, the effects of the 8-week supplementation period with daily 200 mg OPCs or placebo will be investigated on the following secondary study parameters:

1. Plasma nitrite and nitrate levels
2. Systemic oxidative stress markers:
   1. Plasma levels of 8-iso-prostaglandin F2 (PGF2)
   2. TEAC plasma levels
   3. GSH levels in erythrocytes
   4. Oxidative DNA damage in peripheral lymphocytes
   5. Gene expression levels of the redox enzymes superoxide dismutase, glutathione peroxidase, catalase, hemeoxygenase-1 in whole blood.
3. Systemic inflammation markers:
   1. Plasma levels of hsCRP
   2. Plasma levels of fibrinogen
   3. Plasma levels of inflammatory cytokines TNF-, IL-1, IL-6, IL-8 and IL-10.
   4. Concentrations of the cytokines TNF-, IL-1, IL-6, IL-8 and IL-10 after ex-vivo stimulation with lipopolysaccharide (LPS) of whole blood.
   5. Gene expression levels of cytokines (e.g. TNF-, IL-1, IL-6, IL-8, IL-10), adhesion proteins (ICAM‑1), and I-kB- in whole blood.

### Other study parameters

1) Plasma lipid levels:

- 1. High density lipoprotein (HDL)
  2. Low density lipoprotein (LDL)
  3. Very low density lipoprotein (VLDL)
  4. total cholesterol
  5. triglycerides

1. Gene expression levels of enzymes involved in fatty acid catabolism:
   1. Lipoproteinlipase (Lpl)
   2. 3-hydroxy-3-methylglutaryl-CoA-synthase 2 (Hmgcs2)
   3. Enoyl-CoA-hydratase (Ech1)
   4. Acetyl-CoA acyltransferase 2 (Acaa2)
   5. Acetyl-CoA oxidase 1 (Acox1)
   6. Propionyl-CoA carboxylase (Pcca)
2. Platelet reactivity
3. Arginase activity in erythrocytes
4. Plasma concentrations of OPCs and their metabolites
5. Blood pressure

## Randomisation, blinding and treatment allocation

We will allocate the subjects to one of the two treatments in a random manner. Since the amount of cigarettes smoked per day directly reflects the subject’s level of oxidative stress (7), we will balance the groups with respect to the individual smoking habits. This will be achieved by classifying smoking habits in the following manner:

1. 10 – 20 cigarettes per day
2. > 20 cigarettes per day

The study will be carried out in a double-blind fashion, i.e. neither the subject nor the investigators will be aware of the treatment a subject receives.

The identity of the investigational products will be blinded by a numerical code.

The capsules will be packaged in suitable blisters containing the appropriate number of capsules for a 2-week intervention (i.e. 2 x 14 = 28 capsules) of an individual subject. The blisters will be packed in small boxes properly labelled with a unique numerical code.

In addition, three identical envelopes will be prepare each containing again two envelopes with the respective treatment codes.

One envelop will be stored at a secured place where the principal investigator will have direct access; another envelop will be stored at a secured place where the responsible medical doctor will have direct access, and the third envelop will be kept at a secured place at the head of the Toxicology Department’s site.

As soon as a serious adverse event (SEA) will occur during the study period (for definition see chapter 8.2), the responsible medical doctor and the principal investigator are ultimately responsible for the final decision on breaking the code. Only in case of medical urgency, the blinding code can be broken.

If it does not become necessary to break the blinding codes throughout the study, decoding will first take place after a blind review including preliminary statistical analyses of the data of the primary study parameter assessed by the investigators.

In all cases, unblinding will take place under survey of a witness.

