## Study procedures

After signing of the informed consent form before the screening (visit 1), subjects will be invited for further five test sessions at the investigational site.

The test sessions will take place prior to the beginning of the intervention period (visit 2), and after two (visit 3), four (visit 4), six (visit 5) and eight (visit 6) weeks of intervention (see also fig 1).

### Visits 2, 4 and 6

These sessions will be carried out in the Circulation Lab of the Dept. of Internal Medicine, MUMC under supervision of experienced lab assistants and the principle investigator. The lab has gained extensive experience in the performance of forearm blood flow measurements over the past years (76-83).

Subjects will be asked to refrain from smoking and beverages containing caffeine or alcohol for at least 12 hours before the experiments, which will be scheduled at around 8 a.m. after an overnight fast (i.e. no consumption of food and drinks later than 22.00h the evening before the test day except of drinking water).

After arrival in the lab, subjects’ well-being will briefly be checked as well as the occurrence of any adverse event, the use of concomitant medication and compliance to the study protocol based on the notes in their study diary. Consequently, the subjects will receive the Investigational Products for the next 2 weeks (not applicable on visit 6) and the measurements will commence.

The measurements will be carried out in a quite room with a constant temperature of 23°C. The subjects will be studied in the supine position and remain in bed during the experiments. Prior to the vascular function measurements blood pressure will be measured by a suitable automatic device and according to the standard procedure of the Circulation Lab.

1. **Microvascular function measurement**

By means of LDF the superficial skin perfusion will be assessed in the finger before and after local application of ACh (1% Miochol, IOLAB, Bourneville Pharma, Netherlands), a mix of ACh (1%) and L-NMMA (1% Clinalfa, Bachem, Switzerland) and SNP (0.01 Nipride, Roche, Netherlands) via iontophoresis and in accordance with a standard protocol (84, 85).

By means of a low positive current (0.1 mA for 20 s) ACh will migrate across the skin. Seven increasing doses of ACh will be applied locally with an interval of 60 s between each dose.

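### Decoding need not wait for all data to be final, and the emergency code appears to be kept per treatment, so one code break would reveal all 34 allocations

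*Protocol*

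**What the plan says.** All of this is in the protocol; no statistical analysis plan is at hand.

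- **Blinding.** Section 7.2 states that "neither the subject nor the investigators will be aware of the treatment a subject receives". Laboratory staff and the data analyst are not named. On pack labelling it says: "The blisters will be packed in small boxes properly labelled with a unique numerical code".
- **Decoding.** Without an emergency, "decoding will first take place after a blind review including preliminary statistical analyses of the data of the primary study parameter".
- **Form of the code.** "three identical envelopes will be prepare each containing again two envelopes with the respective treatment codes".
- **Custody.** "One envelop will be stored at a secured place where the principal investigator will have direct access". The second set is accessible to the responsible medical doctor, and the third is kept with the head of the department. The medical doctor and the principal investigator are jointly responsible for deciding on a code break after a serious adverse event.
- **Safeguards.** "Only in case of medical urgency, the blinding code can be broken", and "In all cases, unblinding will take place under survey of a witness". Storage is at secured places.
- **Outcome sessions.** Section 7.3.1 places visits 2, 4 and 6, with the FMD and LDF measurements, "under supervision of experienced lab assistants and the principle investigator".

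**The concern.** There are two separate weaknesses.

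The first is the decoding point. Once the code is open, anyone who still has to run assays, resolve queries or settle how a variable is handled can know the allocation. The secondary and other parameters (sections 7.1.2 and 7.1.3) are largely laboratory measurements: cytokines, oxidative DNA damage, gene expression, platelet reactivity, OPC metabolites. If some of these are finished after decoding, their results no longer come from a blinded process. The primary parameter has a related gap. If the preliminary analyses were run by masked group code, the size of the group difference would be visible before the final analysis was fixed.

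The second is the form of the emergency code. A code break is meant to tell the responsible persons what one subject received. If the envelope lists a whole treatment arm, opening it for one subject ends the blind for everyone. One of the persons with access supervises the sessions in which the main outcomes are measured.

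**Working it through.** The plan gives no figure on this point. The check is a reading of the text and a count.

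**Step 1: what must be finished before decoding.** Section 7.2 sets one condition in the absence of an emergency: a blind review that includes preliminary analyses of the primary parameter. Against this:

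- Sections 7.1.2 and 7.1.3 list three numbered groups of secondary parameters and six items or groups of other parameters. Section 7.2 mentions none of them as a condition.
- Section 11.5 ties publication to completion of the sample analyses. It does not tie decoding to it.
- No database lock is named as a condition for decoding.
- Section 7.2 speaks of the primary parameter in the singular, whereas section 7.1.1 names FMD and the LDF responses to ACh, to ACh with L-NMMA and to SNP. Which of these must have been analysed is therefore also unclear.

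The text thus permits decoding while assays are outstanding. It does not say that this will happen.

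**Step 2: what the preliminary analyses show.** Section 9.2 plans a comparison between two groups. Section 7.2 does not say whether the preliminary analyses are pooled or split by masked group, so both readings are open.

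**Step 3: how many subjects one opened envelope reveals.** Inputs: 34 subjects and two arms (section 3), 17 per group (section 4.5), two inner envelopes per set (section 7.2).

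- One envelope per treatment: opening one shows that arm directly (17), and the other arm follows by elimination (17). Exposed: 17 + 17 = 34 of 34.
- Any other division of the 34 subjects over two envelopes: the larger one holds at least 34 / 2 = 17 subjects.
- One envelope per subject: exposed 1 of 34.

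Two inner envelopes therefore cannot give subject-level breaking, unless something further inside is sealed by subject. The section does not mention this.

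**Step 4: what the safeguards do.** Secured storage, the urgency rule and the witness make an improper or casual opening less likely. The numerical code on the boxes keeps treatment from being read off the pack. None of them reduces the number of allocations visible after a proper opening.

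**Step 5: overlap of roles.** The principal investigator has direct access to one set (section 7.2), shares the code-break decision (section 7.2) and supervises the FMD and LDF sessions (section 7.3.1). After one break, the supervisor of the remaining sessions could know every allocation.

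**The case against.** Several stronger readings are tempting, and the protocol does not support them.

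- **That only the primary parameter is reviewed blind.** The text says that the review includes it. That is a minimum, and the review may cover more.
- **That assays will be run unblinded.** The protocol is silent on the order of assays and decoding. It merely fails to rule this out.
- **That the investigators will see a masked group difference and its p value.** This is an inference. Boxes carry unique numbers, and the preliminary analyses may be pooled distribution checks.
- **That test, transformation and exclusions are all freely open at that point.** Section 9.2 sets an order: t-test, then transformation, then Mann-Whitney. The exclusions in section 4.4 are mainly in-study withdrawal criteria, as section 7.4 confirms by referring to them.
- **That the principal investigator takes the measurements.** The text says that this role supervises.

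It can also be said that a code break may never occur. Section 6.2 reports one dropout attributed to the product among 5536 subjects; at that rate, 17 subjects on the active product would give 17 / 5536 = about 0.003 such cases. That rate does not count serious adverse events from any cause in either arm, which are what section 7.2 links to the code-break decision, but it suggests that a break is unlikely. Finally, data lock and the content of a blind review are often left to an analysis plan, and the study calls itself a pilot (section 4.5).

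These points remove any claim that the blind is unprotected. They leave two things standing: the protocol itself fixes a decoding point without requiring final data, and it fixes a form of emergency code that is too coarse.

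**Conclusion.** The point holds in limited form, as a cheap improvement rather than an error that undermines the design. The text does not secure blinding of the secondary and other data through to their completion, and it does not say that the preliminary analyses avoid group codes. One emergency break would expose 34 of 34 subjects instead of 1. The 34 assumes that each inner envelope covers one treatment, which is the plainest reading but is not stated outright; for any other split over two envelopes, the larger one still covers at least 17. Actual harm to the outcome sessions would further require that a break occurs and that the knowledge reaches those who measure or supervise. No bias in any result can be quantified from the protocol.

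**What to change.** Amend section 7.2 as follows.

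1. Hold the blind review on pooled data without any group code, and record the transformations, tests and analysis sets in writing there.
2. Decode only after all primary, secondary and other data are final and locked.
3. Replace the two inner envelopes in each set with one sealed envelope per subject number, so that a break reveals one subject only. Include numbers for replacement subjects, which section 7.5 allows in the first two weeks.
4. Preferably keep the sets with persons who take no part in the outcome sessions or the analysis. This must be reconciled with the principal investigator's stated joint responsibility for code-break decisions; the study team has to settle how.

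The cost is protocol wording and 34 sealed slips per holder, or 3 × 34 = 102 for the three sets, plus any for replacements. The downside is that decoding waits for the last assay.

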## Study procedures

After signing of the informed consent form before the screening (visit 1), subjects will be invited for further five test sessions at the investigational site.

The test sessions will take place prior to the beginning of the intervention period (visit 2), and after two (visit 3), four (visit 4), six (visit 5) and eight (visit 6) weeks of intervention (see also fig 1).

### Visits 2, 4 and 6

These sessions will be carried out in the Circulation Lab of the Dept. of Internal Medicine, MUMC under supervision of experienced lab assistants and the principle investigator. The lab has gained extensive experience in the performance of forearm blood flow measurements over the past years (76-83).

Subjects will be asked to refrain from smoking and beverages containing caffeine or alcohol for at least 12 hours before the experiments, which will be scheduled at around 8 a.m. after an overnight fast (i.e. no consumption of food and drinks later than 22.00h the evening before the test day except of drinking water).

After arrival in the lab, subjects’ well-being will briefly be checked as well as the occurrence of any adverse event, the use of concomitant medication and compliance to the study protocol based on the notes in their study diary. Consequently, the subjects will receive the Investigational Products for the next 2 weeks (not applicable on visit 6) and the measurements will commence.

The measurements will be carried out in a quite room with a constant temperature of 23°C. The subjects will be studied in the supine position and remain in bed during the experiments. Prior to the vascular function measurements blood pressure will be measured by a suitable automatic device and according to the standard procedure of the Circulation Lab.

1. **Microvascular function measurement**

By means of LDF the superficial skin perfusion will be assessed in the finger before and after local application of ACh (1% Miochol, IOLAB, Bourneville Pharma, Netherlands), a mix of ACh (1%) and L-NMMA (1% Clinalfa, Bachem, Switzerland) and SNP (0.01 Nipride, Roche, Netherlands) via iontophoresis and in accordance with a standard protocol (84, 85).

By means of a low positive current (0.1 mA for 20 s) ACh will migrate across the skin. Seven increasing doses of ACh will be applied locally with an interval of 60 s between each dose.

After the last ACh measurement the LDF probe will relocated slightly on the skin to prevent, that potential rests of ACh may influence the measurements with SNP.

Coadministration of ACh and L-NMMA will be done in the same way as described for the ACh application.

SNP will locally delivered by means of a low negative current (0.2 mA for 20 s) in seven increasing doses with an interval of 90 s between each dose.

The ACh and the ACh + L-NMMA measurements will take approximately 10 min.; the SNP measurements will last approximately 15 min.

During all measurements skin temperature will continuously be monitored and regulated by the Laser Doppler probe. The skin temperature has to remain above 28°C.

1. **Conduit artery function measurement**

Endothelial function of conduit vessel will be measured in the bracherial artery of the non-dominant arm, just above the elbow (86, 87). By means of a vessel wall-movement detector system consisting of an ultrasound imager connected to a data acquisition and processing unit arterial diameter and peak flow velocity will be recorded for 3 min. at baseline.

Consequently, a pressure cuff placed around the forearm will be inflated to a supra-systolic pressure (systolic pressure + 40 mmHg) in order to induce forearm ischemia. After 5 min. of sustaining this pressure the cuff will be released. As a consequence blood flows with an increased velocity in the vessel causing an increased shear stress on the endothelium which serves as the stimulus for FMD. The arterial diameter and peak flow velocity will be measured continuously after cuff release for further 240 s. The relative increase in diameter related to the evoked relative increase in blood flow will be used in the statistical analysis (88).

The FMD measurement will take approximately 15 min.

The entire test session will last approximately 2.5 hours in total.

### Visits 3 and 5

For these visits it is not required that the subjects are in a fasted state, because it is not intended to assess any of the study parameters on these occasions. The visits are rather aimed to control the subject’s well-being, the experience of any adverse events, the use of concomitant medication, the compliance with the intake of the investigational product and other relevant study procedures. Also notes in the study diary (see annex 1) will be considered in the discussion. At the end the subjects will receive the Investigational Product for the following 2 weeks.

These sessions will not exceed 30 min.

